**CLASSIFICATION OF PROTOCOL VIOLATION**

Protocol violations were defined in 4.3. We will report protocol violations as:

- Number of patient in interventional group with any protocol violation vs. Number of patient in control group with any protocol violation
- And then detail by type of violation (a. then b.,…), i.e. for protocol violation a. : Number of patient in interventional group with protocol violation type a. vs. number of patient in control group with protocol violation type a.
  1. PRIMARY DATA ANALYSES

5.2.1 Outcome variables

5.2.1.1 Primary outcome

Primary outcome (time to successful extubation) is subjected to competitive risk (death). However, assuming competing risk will be identical in both groups, survival analysis will be done according to a cause-specific analysis (Cox model) with randomization strata as covariate. Hence, primary outcome will be assessed with the Hazard Ratio (HR) produced by Cox model.

Time to event will be:

- For patients successfully extubated: time from inclusion to successful extubation
- For patients who died before successful extubation or Day 90: time from inclusion to death, with censoring at this time point
- For patients not weaned from mechanical ventilation at Day 90 will be censored at this time point.

Two diagnosis will be performed:

1. Proportional hazard assumption will be checked through scaled Schoenfeld residuals statistical test and graphical plot
2. Verification of influential observations: outliers will be identified by 1) plotting deviance residuals and checking symmetrical distribution around zero and 2) plotting the estimated changes in the regression coefficients upon deleting each observation in turn (dfbeta) . In case of influential observation, the observation will be checked for error, corrected if wrong, or conserved if true.

If the proportional hazard assumption is not met, a chronological variable will be used, if possible, otherwise, a log-rank test will be performed.

To account for competing risk, a sensitivity analysis will be performed on the main outcome as follows: the main outcome will be described with cumulative incidence functions and analyzed with a Fine and Gray model with successful extubation as event and death as competitive risk, with randomization strata as covariate. Proportional hazard assumption will be checked by plotting Schoenfeld residuals against event time for each covariate. If the proportional hazard assumption is not met, a chronological variable will be used, if possible.

We will provide graphical representation using a Kaplan Meier curve for the Cox model, depicting the two groups without stratification and a cumulative incidence graph for Fine and Gray model depicting the two groups without stratification, with successful extubation and death as events.

Results will be reported a table with four columns (intervention group, control group, Hazard ratio, p-value). The subgroup analysis will be presented as a forest plot.

In order to express effect size, the median value of the difference between groups in time to successful extubation will be provided (along with its 95% confidence interval).

A second statistician will carry out the analysis of the primary outcome on the dataset.

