In a pilot observational study on 88 patients, median time between first SBT and extubation was 22h with a strategy using SBT-PS and PEEP. We hypothesized that a between-arm difference of at least 24 hours would be clinically relevant to prefer a SBT strategy over one another. With an alpha risk of 5% and a bilateral hypothesis, a power of 80% and a hazard ratio of 2 (based on the ratio of median duration of time between first SBT and successful extubation), a total of 66 successful extubation would be needed. Accounting for both potential deaths before successful weaning and weaning failure (assumed to amount to 30%), we plan to include 94 patients (47 per group).

- 1. STUDY PROCEDURE

|  | Inclusion (day-1) | Day-2 to day-90 | ICU discharge / Death | Day-28 | Day-90 |
| --- | --- | --- | --- | --- | --- |
| Demographic data | X |  |  |  |  |
| Patient weaning readiness | X | X* |  |  |  |
| SBT result | X | X* |  |  |  |
| Arterial blood gas | X | X* |  |  |  |
| *If SBT success* |  |  |  |  |  |
| Cough score | X | X* |  |  |  |
| Abundancy of respiratory secretions | X | X* |  |  |  |
| Extubability criteria | X | X* |  |  |  |
| *If extubation* |  |  |  |  |  |
| Extubation date and time | X** | X** |  |  |  |
| Extubation type (protocolized/self-extubation) | X** | X** |  |  |  |
| Post-extubation NIV characteristics | X** | X** |  |  |  |
| Respiratory physiotherapy characteristics | X*** | X*** |  |  |  |
| High-flow nasal oxygen use | X | X*** |  |  |  |
| Invasive mechanical ventilation status | X | X*** |  |  |  |
| *If reintubation* |  |  |  |  |  |
| Reintubation criteria | X | X |  |  |  |
| *If tracheostomy performed* |  |  |  |  |  |
| Characteristics of tracheostomy |  |  | X |  |  |
| *Follow-up data* |  |  |  |  |  |
| Date/hour of cessation of invasive ventilation and NIV |  |  | X |  |  |
| End of study |  |  |  |  |  |
| Respiratory status |  |  | X | X | X |
| Mortality |  |  | X | X | X |
| *As long as the patient is intubated or tracheostomized  **On the day of extubation and the day after  ***during the 7 days following extubation  NIV denotes non-invasive ventilation, and SBT spontaneous breathing trial. | | | | | |

1. Population of Analysis (intention to treat population)

All subjects who were randomized except patients secondary excluded from the study due to:

- Transfer to another ICU not participating to the study
- Consent withdrawal
- Lack of inclusion criteria or presence of exclusion criteria

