   1. OTHER PARAMETERS

**DEMOGRAPHY AND BASELINE**

**Collected variables**

- Randomization group: categorical variable. Intervention or control group.
- Stratification group: categorical variable. COPD or Chronic heart failure or Other
- Time of inclusion: date variable. Expressed as date (DD/MM/YYYY) and hour (HH:MM)
- Sex: categorical variable. Male or female
- Age: continuous variable. Expressed in years
- Height: continuous variable. Expressed in years, rounded to the nearest integer
- Weight: continuous variable. Expressed in kilos, with a precision of 0.5.
- Body mass index: continuous variable. Expressed in kilos, rounded to the nearest integer
- Hospital admission date: date variable. Expressed as date (DD/MM/YYYY). In case of referral from another hospital, hospital admission date is the date of admission in the previous hospital.
- ICU admission date: date variable. Expressed as date (DD/MM/YYYY). In case of referral from another ICU, ICU admission date is the date of admission in the previous ICU.
- Intubation date: date variable. Expressed as date (DD/MM/YYYY). In case of multiple intubation during ICU stay, the date corresponds the most recent intubation.
- Intubation due to respiratory failure: categorical variable (yes or no)
- Intubation due to hemodynamic failure: categorical variable (yes or no)
- Intubation due to neurological failure: categorical variable (yes or no)
- Intubation due to major surgery: categorical variable (yes or no)
- Intubation due to other reason: categorical variable (yes or no)
- Admission context: categorical variable (medical, planned surgery, emergent surgery, trauma)
- SAPSII score: continuous variable, ranging from 0 to 163
- Respiratory SOFA score, discrete variable, ranging from 0 to 4
- Hemodynamic SOFA score, discrete variable, ranging from 0 to 4
- Hepatic SOFA score, discrete variable, ranging from 0 to 4
- Renal SOFA score, discrete variable, ranging from 0 to 4
- Neurological SOFA score, discrete variable, ranging from 0 to 4
- Hematologic SOFA score, discrete variable, ranging from 0 to 4
- COPD status: categorical variable. None or suspected or proven
- Gold stage: categorical variable. Stage 1, 2,3 or 4. Only for COPD patients.
- Chronic respiratory failure: categorical variable (yes or no)
- Chronic respiratory failure type: categorical variable (obstructive, restrictive or mixed). Only for chronic respiratory failure patients.

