**Computed variables**

- Hospital length of stay at inclusion: continuous variable. Expressed in days, equal to day of inclusion minus day of hospital admission
- ICU length of stay at inclusion: continuous variable. Expressed in days, equal to day of inclusion minus day of ICU admission
- Intubation duration at inclusion: continuous variable. Expressed in days, equal to day of inclusion minus day of intubation
- Total SOFA score, computed as the sum of the respiratory, hemodynamic, hepatic, renal, neurological and hematologic SOFA, discrete variable, ranging from 0 to 24

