**SUBGROUP ANALYSIS**

An exploratory analysis will be performed on the following subgroups, on the primary judgment criterion.

- - - - Randomization strata
      - COVID status (COVID positive vs COVID negative)
      - Median bicarbonates on the day of extubation (lower than median vs. higher than median)
      - PaCO_2_ at the end of SBT ≥ 45 mmHg vs < 45 mm Hg, on the day of extubation
      - Time between intubation and inclusion below vs. greater or equal to its median value
      - Cough score below vs greater or equal to its median value

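### The primary Cox model adjusts for the randomisation strata only; the planned test is valid, but precision available from baseline intubation duration and SOFA, already collected, is left unused

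*Protocol*

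**What the plan says.** Protocol section 5.2.1.1 sets the primary model: "survival analysis will be done according to a cause-specific analysis (Cox model) with randomization strata as covariate". The Fine-Gray sensitivity analysis in the same section also takes the strata as its covariate. No model with further baseline covariates is described.

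Section 4.3 lists the candidates among the demographic and baseline variables. One is "Intubation duration at inclusion: continuous variable. Expressed in days, equal to day of inclusion minus day of intubation". Total SOFA is also computed there, and severity is recorded as "SAPSII score: continuous variable, ranging from 0 to 163". The subgroup list in section 5.1 includes "Time between intubation and inclusion below vs. greater or equal to its median value".

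The sample size (section 2.5) is built as follows: "With an alpha risk of 5% and a bilateral hypothesis, a power of 80% and a hazard ratio of 2", the ratio being "based on the ratio of median duration of time between first SBT and successful extubation", so that "a total of 66 successful extubation would be needed". With 30% assumed not to reach the event, this gives 94 patients, 47 per group. The missing-data paragraph in section 5.1 rules out imputation.

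**The concern.** The strata capture prior disease (chronic heart failure, COPD or chronic respiratory failure, other). They do not capture how ill the patient is at inclusion or how long ventilation has already lasted. Both are plausible predictors of time to successful extubation, and both are known before the allocated strategy starts. With 47 patients per arm in one centre, stratification on prior disease does not prevent chance differences in either.

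In a Cox model, adding a baseline covariate that predicts the outcome usually raises the power of the treatment test. With about 66 events and no reserve in the sample size, a few points of power from data already on the case report form are worth having. The choice must be made in advance: in an open-label trial, covariates added later would look data-driven.

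**Working it through.** **1. The plan's own figure.** From section 2.5: two-sided alpha 0.05, power 80%, HR 2, 1:1 allocation. Schoenfeld's formula gives

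events = (1.960 + 0.842)² / (0.25 × (ln 2)²) = 65.3, rounded up to 66.

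This reproduces the protocol, and 66 events give 80.4% power. For the total, 66 / 0.70 = 94.3 (stated: 94), and 94 × 0.70 = 65.8 expected events. There is no reserve.

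**2. What kind of effect HR 2 is.** The pilot figure is "median time between first SBT and extubation was 22h with a strategy using SBT-PS and PEEP", and the difference of interest is 24 h: (22 + 24) / 22 = 2.09, taken as 2. A ratio of group medians is not conditional on SOFA or intubation duration. The design HR is therefore closer to what the strata-only model estimates. The other reading, HR 2 as covariate-conditional, is shown for comparison.

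**3. Simulation.** The prognostic strength of the omitted covariates is not in the protocol. It is an assumption, expressed as log-HR per SD of the covariate. Common settings: 94 patients, about 66 events when treatment has an effect, three strata, exponential times, independent censoring.

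- Set A: 6,000 trials per scenario, strata shares 20/35/45% (assumed), likelihood-ratio test. The adjusted model has one prognostic and one noise covariate.
- Set B: 2,000 trials per scenario (1,500 for the strata-only reading and the null), strata shares 20/30/50% (assumed), Wald test. The adjusted model has one prognostic covariate.

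Power, strata-only → adjusted, if HR 2 is the strata-only effect:

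| log-HR per SD | Set A | Set B |
|---|---|---|
| 0.3 | 79% → 82% (+3) | not run |
| 0.5 | 79% → 87% (+8) | 78.8% → 86.6% (+8) |
| 0.7 | 79% → 91% (+12) | 81.3% → 92.2% (+11) |

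Power if HR 2 is the covariate-conditional effect:

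| log-HR per SD | Set A | Set B |
|---|---|---|
| 0.3 | 74% → 77% (+3) | 74.4% → 78.2% (+4) |
| 0.5 | 68% → 78% (+10) | 67.2% → 77.4% (+10) |
| 0.7 | 60% → 77% (+17) | 61.6% → 78.4% (+17) |

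With no prognostic value, where the two readings coincide, set A gives 77.3% → 76.5% (-0.8) and set B 76.6% → 76.6%. Three further noise covariates in set B cost 0 to 2 points. The level of about 77% at zero strength, against Schoenfeld's 80.4%, appears in both models, so omitted covariates do not explain it. Freedman's formula, which asks for 71 events, points the same way.

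**4. The hazard ratio.** When the conditional HR is 2, the strata-only HR averages about 1.9, 1.8 and 1.75 in set A, and 2.00, 1.90 and 1.79 in set B, for 0.3, 0.5 and 0.7. The adjusted HR in set B averages 2.07 to 2.09.

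**5. Type I error.** Set A: 5.2 to 5.6% in all models. Set B, at 0.5 and 1.0 per SD: 5.5% and 5.2% strata-only, 6.0% and 5.4% adjusted. The Monte Carlo standard error with 1,500 trials is √(0.05 × 0.95 / 1500) = 0.56 points. Omitting the covariates does not inflate the error rate.

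**6. Model size.** Treatment (1) + strata (2) + two covariates (2) = 5 parameters, and 66 / 5 = 13.2 events per parameter.

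**The case against.** The strongest reply is that nothing here is wrong. Adjusting for the stratification factors is a coherent, pre-specified analysis with a valid test, and further covariates are a matter of efficiency. That stands, and the point is put only as an efficiency improvement. It is not merely a detail left to an SAP that is not shown, because section 5.2.1.1 itself fixes the covariate list of the primary model.

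Three stronger readings are tempting, and the protocol supports none of them.

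- A reader might infer that the strata-only HR is biased toward 1. It lies nearer 1 than the conditional HR because the hazard ratio is non-collapsible: the two models estimate different effects. Chance imbalance does not invalidate the test either, since the p-value and interval already allow for it.
- A reader might infer that the trial is underpowered against its plan. That needs HR 2 to be covariate-conditional. Section 2.5 takes it from a ratio of medians, and on that reading strata-only power is 79 to 81%.
- A reader might infer that the covariates are known to be strong predictors. The protocol gives no figure. Listing time since intubation as a subgroup concerns effect modification and does not show prognostic strength. All patients are judged ready for weaning evaluation and have failed a first T-piece trial, which may narrow the spread of severity.

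Two further cautions stand. The simulations describe neither a mis-specified covariate form nor correlation between the covariates and the strata; overlap with the strata would shrink the gain. And section 2.2 describes randomisation partly in the past tense. If enrolment has begun, changing the primary model of an open-label trial has some cost in credibility, so the change must be documented before unblinded data are seen.

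**Conclusion.** The point holds as a cheap gain in precision, not as an error in the plan. The planned test is valid and its stated power is not missed.

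For an assumed prognostic strength of 0 to 0.7 log-HR per SD, adjustment changes power by about -1 to +12 points if HR 2 is the strata-only effect, which is the reading that section 2.5 suggests. If HR 2 is covariate-conditional, the change runs up to about +17 points. The trade is lopsided: about 1 to 2 points at most are lost if the covariates carry no information, against roughly 8 to 10 points gained at a moderate 0.5 per SD. The size rests wholly on the assumed strength and on the simulation settings (exponential times, independent censoring, assumed strata shares).

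**What to change.** In section 5.2.1.1, before unblinded data are seen, specify the primary Cox model as treatment + randomisation strata + log(intubation duration at inclusion + 1 day) + baseline total SOFA. Keep both added covariates continuous and use the same covariates in the Fine-Gray model. Name total SOFA outright; leaving SOFA or SAPS II as alternatives would reopen the choice. Name the test of treatment too: the likelihood-ratio test is the one for which 5.2 to 5.6% type I error was obtained. Keep the strata-only Cox model as a sensitivity analysis. Do not use the day-of-extubation bicarbonate or PaCO2 values from the subgroup list, because they arise after randomisation.

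In the missing-data paragraph of section 5.1, add an explicit exception: a missing baseline covariate is filled with the overall baseline mean, both arms pooled, so that no patient drops out of the model. Outcomes remain unimputed.

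The cost is a short amendment to two sections and no new data collection. The model gains two parameters (five in total for about 66 events), with at most about 1 to 2 points of power lost if the covariates are not prognostic. The primary HR becomes conditional on these covariates and, if they are prognostic, lies somewhat further from 1 than the strata-only HR, which is still reported. The difference in time to extubation already planned at the end of section 5.2.1.1 is unaffected.

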5.2.1.2 Secondary outcomes

Analysis will be carried out as described in 5.1. Results will be reported a table with four columns (intervention group, control group, univariable absolute difference with 95% confidence interval, p-value).

5.2.2 Flow-chart, baseline and demographic data

A flow-chart will describe:

- Number of patients admitted to the ICU during study period
- Number of patients with more than 24h of mechanical ventilation
- Number of patients with at least 1 SBT (screened population)
- Number of patients without inclusion criteria
- Number of patients with exclusion criteria
- Number of patients eligible (i.e with inclusion and exclusion criteria and causes of non-inclusion)
- Number of patients included and randomized
- Number of patients secondary excluded and cause of exclusion
- Number of patients included in the analysis
- Number of lost to follow-up

Baseline and demographic data will be reported in a table with two columns (intervention group, control group). No comparison will be performed for baseline and demographic characteristics since the study is randomized.

5.2.3 Protocol violations

Analysis will be carried out as described in 5.1.

5.2.4 Daily assessments

Multiple analyses will be performed (methodology described in 5.1)

1. Description of daily assessments for the successful extubation.

The population of analysis will be patients that were successfully extubated. We will report (cf. 4.3):

- - SBT data (on the day of extubation)
  - extubation data
    - Extubation type
    - Post-extubation prophylactic NIV characteristics. Duration of NIV will be computed as the sum of NIV duration on the day of extubation and the following day
    - Post-extubation rescue NIV (during the 7 days following extubation
    - Post-extubation high-flow nasal oxygen (during the 7 days following extubation)
    - Respiratory physiotherapy (during the 7 days following extubation)

Results will be reported a table with four columns (intervention group, control group, p-value).

1. Description of reintubation episodes:

The population of analysis will be patients that experienced reintubation. Since patients can experience multiple reintubations, we will report the number of patients involved and the total number of reintubation. We will not correct for repeated measures. We will report:

- Reintubation data (cf. 4.3)
- Time elapsed since extubation: continuous variable (hours), equals to date/time of reintubation minus date/time of extubation

Results will be reported a table with four columns (intervention group, control group, univariable absolute difference with 95% confidence interval, p-value).

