   1. PRIMARY OBJECTIVE

Main objective: to evaluate whether if an assisted weaning strategy based on SBT-PS with PEEP followed by an SBT-TP to identify patients at high risk of extubation failure and trigger the use of prophylactic post-extubation NIV (assisted weaning strategy, intervention group) leads to a **shorter time to successful extubation** in difficult to wean patients as compared to a weaning strategy based solely on SBT-TP (unassisted weaning strategy, control group) and prophylactic post-extubation NIV based on international guidelines

- 1. SECONDARY OBJECTIVES

1. To evaluate whether if an assisted weaning strategy leads to a higher rate of first successful extubation in difficult to wean patients as compared to an unassisted weaning strategy.
2. To evaluate whether if an assisted weaning strategy leads to a shorter duration of invasive mechanical ventilation in difficult to wean patients as compared to an unassisted weaning strategy.
3. To evaluate whether if an assisted weaning strategy leads to a shorter duration of mechanical ventilation (i.e., invasive and non-invasive) in difficult to wean patients as compared to an unassisted weaning strategy.
4. To evaluate whether if an assisted weaning strategy leads to more ventilator-free days (VFD) at day-28 and at day-90, respectively, in difficult to wean patients as compared to an unassisted weaning strategy.
5. To evaluate whether if an assisted weaning strategy leads to a shorter intensive care unit stay in difficult to wean patients as compared to an unassisted weaning strategy.
6. To evaluate whether if an assisted weaning strategy leads to a shorter hospital stay in difficult to wean patients as compared to an unassisted weaning strategy.
7. To evaluate whether if an assisted weaning strategy leads to a lower mortality in intensive care unit (ICU), mortality at day-28 and mortality at day-90, respectively, in difficult to wean patients as compared to an unassisted weaning strategy.
8. To evaluate whether if an assisted weaning strategy leads to a higher reintubation rate in difficult to wean patients as compared to an unassisted weaning strategy.
9. Background/Introduction

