   - VFD = 28-x for VFD at day-28 or VFD = 90-x for VFD at day-90 if the patient is successfully weaned from invasive mechanical ventilation, with x being the number of days from inclusion to last successful extubation. Successful weaning from mechanical ventilation will be defined as extubation without reintubation within at least 7 days (or weaning from mechanical ventilation for at least 7 days for patients with tracheostomy)
   - VFD = 0 if the patient is mechanically ventilated for more than 28 days after inclusion for VFD at day-28, or more than 90 days after inclusion for VFD at day-90
5. ICU stay (days): ICU length of stay between inclusion and ICU discharge
6. Hospital stay (days): hospital length of stay between inclusion and hospital discharge (to home or rehabilitation facility).
7. ICU, day-28, and day-90 mortality: defined as the ratio of the number of death over each period over the total number of patients per group.
8. Reintubation rate: number of patients with any reintubation divided by the number of patients per group

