  - Post-extubation rescue NIV (during the 7 days following extubation): categorical variable. No, per protocol, protocol violation
  - Post-extubation high-flow nasal oxygen (during the 7 days following extubation): categorical variable. No, Yes
  - Respiratory physiotherapy (during the 7 days following extubation): categorical variable. No, manual therapy, instrumental therapy
- Reintubation (reintubation data): categorical variable. Yes or no
  - Reintubation criteria: categorical variable. Neurological, Hemodynamic, other, Respiratory
  - In case of respiratory criteria reintubation, aetiology: categorical variable:
    - Respiratory exhaustion: Yes or no
    - Abundant respiratory secretion: Yes or no
    - Pneumonia: Yes or no
    - Cardiac pulmonary edema: yes or no
    - Laryngeal dyspnea: yes or no
  - Reintubation for general anaesthesia lasting less than 24h: categorical variable. Yes or no
- Status at the end of the day:
  - Respiratory status: categorical variable: yes or no
  - Weaning protocol: categorical variable: pursuit or end
  - Weight: continuous variable. Expressed in kg, with a precision of 0.5

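### Cause and timing of reintubation are tested between arms only among reintubated patients; respiratory reintubation is never formally compared per randomised patient

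*Protocol*

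**What the plan says.** Section 5.2.4 describes reintubation episodes in a restricted group: "The population of analysis will be patients that experienced reintubation". On the unit of counting it says "Since patients can experience multiple reintubations, we will report the number of patients involved and the total number of reintubation", and then "We will not correct for repeated measures".

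Two kinds of variable go into the table:

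- The reintubation data of section 4.3: cause ("Reintubation criteria: categorical variable. Neurological, Hemodynamic, other, Respiratory") and, for respiratory cases, the aetiology.
- Timing: "Time elapsed since extubation: continuous variable (hours), equals to date/time of reintubation minus date/time of extubation".

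The heading calls this a description, but the output is inferential: "Results will be reported a table with four columns (intervention group, control group, univariable absolute difference with 95% confidence interval, p-value". Section 5.1 supplies the tests, sets significance at 0.05 two-sided, makes no multiplicity adjustment, and asks for absolute as well as relative frequencies.

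Reintubation is compared on all patients elsewhere. Secondary outcome 8 in section 4.2 is "Reintubation rate: number of patients with any reintubation divided by the number of patients per group", and the number of reintubations is a tertiary outcome (section 5.2.5). Neither is split by cause. Section 3 states that every analysis uses the population it labels intention to treat, which does not fit the subset in 5.2.4.

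**The concern.** Being reintubated is a post-randomisation outcome, and the protocol itself allows that the strategy changes it. Secondary objective 8 is "To evaluate whether if an assisted weaning strategy leads to a higher reintubation rate in difficult to wean patients". If the arms differ in who is reintubated, the two groups of reintubated patients are no longer comparable by randomisation. A share of causes among them answers how the causes are mixed; it does not answer how often each cause occurs in patients assigned to each strategy.

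Cause matters in this trial. Under section 2.4, an assisted-arm patient who passes the pressure-support trial can be extubated after failing the T-piece trial, whereas a control patient must pass the T-piece trial. Respiratory reintubation is thus the harm closest to the contrast under study, yet its only formal comparison uses a denominator that cannot measure its frequency. Time since extubation has the same problem. If extra episodes follow the same time distribution, the median does not move; if they come late, it lengthens and looks better.

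**Working it through.** **Figures the plan gives.** None concerns the reintubation comparison. The trial size reproduces: 4 × (1.960 + 0.842)² / (ln 2)² = 65.3, so 66 events, and 66 / 0.70 = 94.3, stated as 94 (47 per group). Nothing below alters these.

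**Inputs.** 47 per arm (section 2.5). All reintubation rates and counts are assumptions, because the protocol states none. One reintubation per patient is assumed, which is simpler than the plan, since the plan allows several.

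**The identity.** With one reintubation per patient, respiratory rate = respiratory share among reintubated × all-cause rate. Two results follow.

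1. If the assisted arm has a higher respiratory rate but a lower share, its all-cause rate must be higher.
2. Let control have respiratory rate r and other-cause rate o, and let the assisted arm have 2r and o′. The assisted share is equal or lower when 2r/(2r + o′) ≤ r/(r + o), that is, when o′ ≥ 2o. The share looks equal or better only if other causes at least double as well.

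**Fixed counts, respiratory reintubation doubled from 6 to 12 (Fisher tests).**

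| Other causes | Share, control v assisted | All-cause rate, control v assisted |
|---|---|---|
| Also double | 6/8 v 12/16: 75% v 75%, p = 1.00 | 17.0% v 34.0%, p = 0.097 |
| More than double | 6/8 v 12/18: 75% v 66.7%, p = 1.00 | 17.0% v 38.3%, p = 0.037 |
| Unchanged | 6/9 v 12/15: 66.7% v 80%, p = 0.64 | 19.1% v 31.9%, p = 0.24 |

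In every row the per-patient comparison is 6/47 = 12.8% v 12/47 = 25.5%, a difference of +12.8 points. The standard error is √(0.128 × 0.872/47 + 0.255 × 0.745/47) = 0.080, so the 95% interval is about −2.9 to +28.5 points; Fisher p = 0.19.

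**Simulation (200,000 trials, 47 per arm).** "Reversed" means that the share favours the assisted arm while the respiratory rate per patient is higher in it.

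| Control (respiratory + other) | Assisted | Mean share difference | True rate difference | Reversed | Reversed trials with higher all-cause rate in assisted arm |
|---|---|---|---|---|---|
| 10% + 5% | 20% + 10% | 0 | +10 points | 40% | 100% (median +17 points) |
| 10% + 4% | 20% + 12% | −9 points | +10 points | 55% | 100% (median +19 points) |
| 10% + 5% | 20% + 5% | +13 points | +10 points | 20% | 100% (median +13 points) |

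The 100% is the identity at work.

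**Precision of the planned comparison.** In the first scenario about 14 v 7 patients are reintubated, with a share of 67% in both arms. The half-width is 1.96 × √(0.222/14 + 0.222/7) = 0.43, or ±43 points.

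**The case against.** A reader might infer that the plan could conceal a doubling of respiratory reintubation. The protocol does not support that. Section 5.1 requires absolute frequencies and 5.2.4 requires the numbers of patients and episodes, so a table showing 6 v 12 respiratory cases beside known arm sizes reveals the doubling. Secondary outcome 8 compares all-cause reintubation on all patients, and a reversed share combined with more respiratory reintubation always comes with a higher all-cause rate in the assisted arm.

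The scenarios in which the share is flat or favourable on average also need non-respiratory reintubation to double or triple, which fits poorly with a specifically respiratory hazard. Where only the respiratory cause rises, the planned table points the right way on average. An interval of ±43 points would reassure few readers, and a reversed difference with p < 0.05 occurred in only about 0.1% and 0.5% of trials in the first two scenarios. The table is descriptive in title and lies outside the primary and secondary outcomes.

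All of this stands and limits the point. It does not justify the p-values. The all-cause comparison cannot attribute an excess to respiratory cause, and it may well miss significance: power is about 47% for 8 v 16 of 47. The difference and interval that answer the cause-specific question are not specified anywhere.

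**Conclusion.** The point holds in a limited form. The differences, intervals and p-values that 5.2.4 orders for cause, aetiology and timing of reintubation do not estimate an effect of the randomised strategy, and leaving repeated episodes uncorrected weakens the p-values further. Respiratory reintubation per randomised patient is not formally compared anywhere. The harm would still be visible through secondary outcome 8 and the reported counts, so the consequence is a misdirected test in a low-stakes table.

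The size depends wholly on assumed rates and on one reintubation per patient. The planned share difference ranges from −9 to +13 points on average against a true +10, with the sign reversed in 20% to 55% of trials. Repeated episodes were not modelled. Changing the denominator gives a correctly targeted estimate but no useful gain in power (about 35% for 6 v 12 of 47).

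**What to change.** In the reintubation item of section 5.2.4:

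- For each cause, respiratory first, report the number of patients with at least one such reintubation over all patients in the arm (the denominator of secondary outcome 8), with the absolute difference and 95% confidence interval. Counting patients also removes the repeated-episode problem from this comparison.
- Keep the episode-level table and time since extubation as description by arm, without a between-arm difference or p-value.
- Reconcile section 3 with 5.2.4 by stating that descriptive tables may use subsets while between-arm inference uses the analysis population.

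The cost is a sentence or two and a changed denominator. No new data are needed, and the 66 events and 94 patients are unaffected. What is lost is a set of p-values on a descriptive table.
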